## Abstract

**Background:**

Approximately 2 million Chinese people die annually from tobacco-related diseases, mostly men; yet, fewer than 8% of Chinese smokers ever receive any smoking cessation advice or support. A social network–based gamified smoking cessation intervention (*SCAMPI: Smoking Cessation App for Chinese Male: Pilot Intervention*) is designed to help Chinese male smokers to quit smoking.

**Objective:**

This paper aims to present the protocol of a study examining the preliminary effectiveness of SCAMPI by comparing the prolonged abstinence rate of a group of users with a comparator group during a 6-week follow-up period.

**Methods:**

A two-arm pilot randomized controlled trial was conducted to assess the preliminary effectiveness and acceptability of the SCAMPI program as a smoking cessation intervention. After initial web-based screening, the first 80 eligible individuals who had gone through the required registration process were registered as participants of the trial. Participants were randomly allocated to the intervention group (n=40) and the control group (n=40). Participants in the intervention group used the full version of the SCAMPI program, which is a Chinese smoking cessation program developed based on the Behavior Change Wheel framework and relevant smoking cessation and design guidelines with involvement of target users. The program delivers a range of smoking cessation approaches, including helping users to make quitting plans, calculator to record quitting benefits, calendar to record progress, gamification to facilitate quitting, providing information about smoking harms, motivational messages to help users overcome urges, providing standardized tests to users for assessing their levels of nicotine dependence and lung health, and providing a platform to encourage social support between users. Participants in the control group used the restricted version of the SCAMPI program (*placebo app*).

**Results:**

Recruitment for this project commenced in January 2019 and proceeded until March 2019. Follow-up data collection was commenced and completed by June 2019. The primary outcome measure of the study was the 30-day bio-verified smoking abstinence at the 6-week follow-up (self-reported data verified by the Nicotine Cotinine Saliva Test). The secondary outcome measures of the study included participants’ cigarette consumption reduction (compared baseline daily cigarette consumption with end-of-trial daily cigarette consumption), participants’ 7-day smoking abstinence at 4-week and 6-week follow-up (self-reported), participants’ 30-day smoking abstinence at 6-week follow-up (self-reported data only), and participants’ acceptability and satisfaction levels of using the SCAMPI program (measured by the Mobile App Rating Scale questionnaire).

**Conclusions:**

If the SCAMPI program is shown to be preliminary effective, the study will be rolled out to be a future trial with a larger sample size and longer follow-up (6 months) to identify if it is an effective social network–based tool to support Chinese male smokers to quit smoking.

**Trial Registration:**

Australian New Zealand Clinical Trials Registry ACTRN12618001089224; https://www.anzctr.org.au/Trial/Registration/TrialReview.aspx?id=375381

**International Registered Report Identifier (IRRID):**

RR1-10.2196/18071

## Introduction

### Burden of Tobacco Smoke

Every year, approximately 2 million Chinese people are killed by tobacco-caused diseases [1]. Still, nearly 300 million Chinese people continue to use tobacco each day [1]. Among these smokers, 95% are male [2]. Tobacco use caused 25% of Chinese male deaths [1]. In addition to health harm, tobacco use in China also leads to societal harm [1]. The economic cost of smoking in China amounts to ¥393 billion yuan (US $57.4 billion dollars) per year [1]. This includes direct costs related to health care expenditures and indirect costs related to lost productivity due to early mortality and morbidity [1].

According to the 2010 Global Adult Tobacco Survey in China, 36.4% of Chinese smokers had tried to quit in the past 12 months, whereas 91.8% of them had never received any smoking cessation services [3]. A survey in 2014 found that over half of Chinese smokers never received any quit smoking advice from their health professionals [4]. Since 2006, although some smoking cessation clinics had been set up and the National Quitline had launched, due to limited exposure and accessibility, they have rarely been used by Chinese smokers [5].

### Mobile Smoking Cessation

A 2019 Cochrane review of mobile phone–based interventions for smoking cessation demonstrated the effectiveness of mobile technology in supporting smoking cessation [6]. The most recent World Health Organization report on the global tobacco epidemic indicated that personalized smoking cessation advice and support from mobile phone messages can be a cost-effective tool contributing to address the public health problem of tobacco use [7]. Mobile phone–based smoking cessation interventions have proven to be a cost-effective tool for supporting smokers to quit smoking. Some studies also showed that mobile smoking cessation apps can create short-term impacts on helping smokers to quit smoking [8-13]. A recent study has shown that daily smokers using a behavioral, decision-aid smartphone app achieved 23.8% self-reported 3-month continuous abstinence [14].

The 2017 Connected Consumer Survey conducted by Google Inc noted that 83% of Chinese people use smartphones [15]. China is regarded as the fastest growing smartphone market in the world, with a 10% increase in smartphone penetration rate in the past 5 years [16]. China has the largest smartphone user group (n>700 million people) in the world [17]. Among all the functions and apps of smartphones, WeChat is the most popular app (social network platform) in China. In 2020, 1.2 billion people were monthly active users of WeChat [18]. WeChat users are highly engaged with the app; nearly 80% of WeChat users use the app for >30 min daily [18]. WeChat has become a major tool in communication, entertainment, and payment for Chinese smartphone users.

### Aim of the Study

As previously mentioned, Chinese males are the largest smoking population group in the world. Most Chinese smokers have limited access to smoking cessation services. The lack of appropriate smoking cessation services and limited accessibility to current smoking cessation support lead to a low smoking cessation success rate [19]. The high smartphone penetration rate and usage rate in China provide a great opportunity for developing and implementing smartphone app–based smoking cessation interventions. The potential for WeChat-based smoking cessation interventions to impact and reach out to millions of Chinese smokers is possible like never before.

The prevalence of cigarette smoking in Chinese males is substantial, and mobile smoking cessation programs hold much promise to provide cost-effective support to help smokers to quit. To date, there have been no reported investigations on the efficacy of delivering a smartphone social network–based smoking cessation intervention for Chinese male smokers via a social network platform.

The aim of this study is to introduce the SCAMPI program, which was designed to support Chinese male smokers to quit smoking and present the protocol of a pilot randomized controlled trial (RCT) that assesses the preliminary effectiveness of the SCAMPI program. The study examines the quit rates of abstaining users of the full version SCAMPI program versus the quit rates of a comparator group for a 6-week period. The pilot trial’s main hypothesis is that users of the full version program will have higher biochemical verified 30-day smoking abstinence during the follow-up measures in comparison with the comparator group.

## Methods

### Study Design

This study will be a pilot, two-arm, parallel RCT. We will evaluate the preliminary effectiveness and acceptability of our SCAMPI program as well as recruitment and retention for estimating the sample size of a future definitive trial. All trial procedures will be conducted web-based via WeChat (Tencent). Ethical approval was granted by the University of Auckland Human Participants Ethics Committee (reference number: 021649) and the Zhejiang University School of Public Health Research Ethics Committee (reference number: ZGL201801-2).

### Study Setting

The study setting of this pilot trial will be completely online via the social network platform WeChat. The SCAMPI program will not need to be downloaded or installed on participants’ mobile phones, but they will be authorized to use the program via the WeChat platform.

### Participants

#### Eligibility Criteria

Chinese male smokers will be eligible for inclusion in the study if they indicate at screening that they are smokers (both daily smokers *smoking any types of tobacco products on a daily basis* or occasional smokers *smoking any types of tobacco products occasionally [at least once in a week]*) aged between 25 and 44 years [5], have access to a smartphone, have a WeChat account, have adequate knowledge of Chinese language, and are willing to participate in the study and provide follow-up information at scheduled points of the study. People will be excluded from the sample if they report in the screening test that they are involved in any other types of smoking cessation interventions.

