### Primary Outcome Measure

The primary outcome of this pilot trial will be the participants’ biochemical verified 30-day smoking abstinence at 6-week follow-up. At the 6-week time point, researchers will review participants’ (in both groups) self-reported smoking status in the past 30 days to identify their self-reported 30-day smoking abstinence. The 30-day smoking abstinence is usually used as the primary outcome measure for smoking cessation intervention trials recommended by the Society for Research on Nicotine and Tobacco [35]. Quit failure was defined as any cigarettes smoked in the past 30 consecutive days. This measurement is also known as the 10th level of smoking abstinence in the Chinese standard for smoking cessation [23].

At the 6-week time point, a nicotine cotinine saliva test kit will be sent to participants (in both groups) who report themselves with 30-day smoking abstinence to verify their smoking abstinence status. These participants will be requested to complete the test at home (clear instruction provided) and upload a photo or a short video of the strip test results to the SCAMPI OA. The cotinine test has proven to be a valid and reliable method to test saliva samples for verification of smoking status [36,37].

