### Secondary Outcome Measures

The secondary outcomes of the study included participants’ tobacco consumption changes through the trial period, retention of the trial, program (both versions) usage, and users’ satisfaction with the program (only for intervention group participants).

Tobacco consumption changes include measures of the following:

Participants’ cigarette consumption reduction: Participants will be required to provide their daily cigarette consumption (as a categorial range such as “1 to 5 sticks cigarettes per day”) at the baseline assessment. By using these data to compare with their daily smoking status through the pilot trial, researchers will be able to identify the reduction in cigarette consumption of participants (in both groups). Participants who reduce their consumption by at least one category (eg, from “16 to 20 sticks of cigarettes per day” to “10 to 15 cigarettes per day”) from baseline will be counted as successfully achieving smoking reduction.7-day smoking abstinence at 4-week and 6-week follow-up: At the 4-week and 6-week time points, researchers reviewed and analyzed participants’ (in both groups) smoking status in the past 7 days to identify their 7-day smoking abstinence at both these time points. A 7-day smoking abstinence is defined as not a single cigarette being smoked in the past 7 days [35].30-day self-reported smoking abstinence at 6-week follow-up: At the 6-week time point, researchers will review and analyze participants’ smoking status in the past 30 days to identify their self-reported 30-day smoking abstinence. A 30-day smoking abstinence is defined as not a single cigarette being smoked in the past 30 days [35].

The retention rate of the trial refers to participants providing their daily smoking status at the end of every week.

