**Secondary outcomes**				
	Cigarette consumption	✓	✓	✓
	7-day smoking abstinence at 4-week and 6-week follow-up	—	✓	✓
	30-day self-reported smoking abstinence at 6-week follow-up	—	✓	✓
	Participants’ retention	✓	✓	✓
	Program usage	—	✓	✓
	Users’ satisfaction with the program (intervention group)	—	—	✓

^a^Data were collected in the described timepoint.

^b^Data were not collected at the described timepoint.

Screening data will be collected at week 1 (day 0) via the registration questionnaire to determine eligibility for all individuals who read the study advertisement and entered the study registration system. The questionnaire consists of a short overview of the aim of the study and questions regarding the person’s demographics, additions, quitting history, willingness to quit, and the usage of other smoking cessation interventions. All questionnaires of the trial were delivered by the Tencent Questionnaire platform, which is compatible to the WeChat platform.

Data on participants’ cigarette consumption will be collected from day 1 to day 42 of the study via the same questionnaire platform. At the end of each week, participants will be provided with a link through WeChat messages to have access to the corresponding online questionnaire to enter their cigarette consumption status on each day of the week.

Users’ satisfaction with the SCAMPI program (intervention group only) will be collected on day 42 along with the last weekly cigarette consumption status checking questionnaire. Data collected through online questionnaires will be downloaded from the platform and stored in a secure university server after every collection.

The program usage data (both versions) will be recorded by the WeChat mini-program and OA databases. These data will be exported and stored in the same place as data collected from online questionnaires.

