### Power

We determined the power for the proposed main trial of this study. A total sample size of 530 (265 per group) will have 90% power at 5% significance (two-sided) to detect an absolute difference of 10% on the primary outcome between the 2 groups, assuming a control rate of 6.7% [19] and 20% loss to follow-up. Given the budget and resource limitations, in this study, we aim to recruit around (80/530, 15.1%) of the total sample size required for the main trial, that is, n=80 (40 per group), using an open recruitment strategy to recruit all participants within a month. At the end of the study, we will re-estimate the power of the final percentage differences between groups in the effectiveness report to further determine the exact final sample size of a full trial. The sample size is considered as a major limitation of the study.

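### Entry covers smokers of any tobacco product, but abstinence and the weekly form are worded by cigarettes alone, which mainly affects the self-reported outcomes

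*Protocol article*

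**What the plan says.** Under Eligibility Criteria, the protocol article accepts two kinds of smoker: those "smoking any types of tobacco products on a daily basis" and those "smoking any types of tobacco products occasionally [at least once in a week". Neither is limited to cigarettes.

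The outcomes are worded differently:

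- Primary Outcome Measure: "Quit failure was defined as any cigarettes smoked in the past 30 consecutive days".
- Secondary Outcome Measures, 7-day (weeks 4 and 6): "A 7-day smoking abstinence is defined as not a single cigarette being smoked in the past 7 days".
- Secondary Outcome Measures, 30-day self-report (week 6): "A 30-day smoking abstinence is defined as not a single cigarette being smoked in the past 30 days".
- Data Collection, weekly questionnaire: participants "enter their cigarette consumption status on each day of the week".

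The primary outcome has a further step. At week 6, "a nicotine cotinine saliva test kit will be sent to participants (in both groups) who report themselves with 30-day smoking abstinence". The test is done at home and a photo or short video of the result is uploaded. The three self-reported abstinence outcomes have no such step.

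**The concern.** Entry and outcome describe different behaviours. A participant can qualify through tobacco that the outcome definitions never ask about. Two kinds of men are then misclassified: one who smokes only other tobacco, who meets the abstinence definitions without changing anything, and one who gives up cigarettes but keeps other tobacco, who is recorded as having quit.

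Randomisation should spread such men evenly on average, so the expected effect is not bias towards one arm. Abstinence rises in both arms and the difference between them shrinks. This matters beyond the pilot, because the Power section says that the observed percentages will be used to settle the size of the full trial.

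A second, smaller issue is that weekly smoking is enough for entry while one secondary outcome looks back only 7 days. A weekly smoker can show a smoke-free window without having changed.

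**Working it through.** **1. How the written rules classify a man**

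| Man | Self-reported 7-day and 30-day outcomes | Primary outcome |
|---|---|---|
| Smokes only non-cigarette tobacco, unchanged | Abstinent | Passes self-report; result then depends on cotinine |
| Drops cigarettes, keeps other tobacco | Abstinent | Passes self-report; result then depends on cotinine |
| Smokes a cigarette about once a week, unchanged | 30-day: almost always a failure; 7-day: see step 4 | Almost always a failure |

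No section limits entry to cigarette smokers or extends abstinence to other tobacco.

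**2. The plan's own sample size**

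The Power section gives a control rate of 6.7%, a 10-point difference (so 16.7%), two-sided 5%, 90% power and 20% loss. With unpooled variance:

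n = (1.960 + 1.282)² × [0.067 × 0.933 + 0.167 × 0.833] / 0.10² = 10.507 × 0.2016 / 0.01 = 211.9, so 212 per group.

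212 / 0.80 = 265 per group, 530 in total. This is the stated figure and it is not in dispute.

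**3. Effect of false abstainers on that figure**

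The article gives no share of men who smoke other tobacco, so a range is assumed. If a fraction f of each arm is counted abstinent regardless, each rate becomes p(1 − f) + f and the difference becomes 10(1 − f) points. Numbers needed use the formula in step 2; power uses the pooled normal approximation with 212 evaluable per group.

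| f (assumed) | Rates | Power | Needed per group with 20% loss | False abstainers per 40 in the pilot |
|---|---|---|---|---|
| 0% | 6.7% v 16.7% | 0.90 | 265 | 0 |
| 1% | 7.6% v 17.5% | 0.87 | 289 | 0.4 |
| 2% | 8.6% v 18.4% | 0.84 | 313 | 0.8 |
| 5% | 11.4% v 20.9% | 0.76 | 388 | 2 |
| 10% | 16.0% v 25.0% | 0.63 | 524 | 4 |

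For comparison, the stated control rate implies 40 × 0.067 = 2.7 quitters in the pilot control arm. The table describes an outcome without biochemical verification. For the primary outcome it is an upper bound, because cotinine should remove most regular users.

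**4. Smoke-free 7-day windows in an unchanged once-a-week smoker**

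- *Evenly spaced, every 7 days:* every 7-day window contains one occasion, so the chance of a clear window is 0%.
- *One random day in each calendar week:* if the trial week is offset by k days, the chance is (k/7) × ((7 − k)/7) = k(7 − k)/49. For k = 0 to 6 the numerators are 0, 6, 10, 12, 12, 10, 6, which sum to 56. The average is 56/(7 × 49) = 16%, and the maximum is 12/49 = 24%.
- *Fully random times averaging one a week:* exp(−1) = 37%.

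Over 30 days, the fully random model gives exp(−30/7) = 1.4%. The one-day-per-calendar-week model gives zero, because any 30-day window contains at least three whole calendar weeks. The point therefore reaches only the 7-day outcome.

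**The case against.** The strongest reply is that the primary outcome is biochemically verified. Cotinine reflects nicotine intake rather than cigarettes as such, so a regular user of other tobacco should test positive and be counted as smoking. That stands. A reader might infer from the quit-failure sentence that the primary outcome is judged on cigarettes alone. The article does not support this, since everyone in either arm who reports 30-day abstinence is sent a kit. What remains is narrower. It is a single home test arranged from day 42, the article gives no cut-off or detection window, and how often it would miss an infrequent user cannot be judged. The written definition and the test can also disagree: a man who smokes only other tobacco is not a quit failure by the wording, yet a positive test would fail him.

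A second reply is that someone who smokes at least weekly, as the entry rule says, smokes in about every 7-day window. That is fair, and it is why 37% is the top of a range and not an estimate.

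Third, a reader might infer that randomisation or the analysis should have been stratified by daily or occasional smoking. Unstratified blocks are a normal choice for 80 participants, the number of occasional smokers is not given, and covariates may be covered in an analysis plan that is not shown. This is not a defect of the article.

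Nor is the lack of cotinine for the secondary outcomes an error in itself: the 30-day version is openly labelled as self-reported and sits beside its verified counterpart.

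Finally, cigarettes may simply be shorthand for smoking. That is possible, but the entry criteria name all tobacco types explicitly, and nothing in the article says that the outcome wording should be read as broadly.

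**Conclusion.** The mismatch between entry and outcome wording is in the text and is not resolved elsewhere in the article. It bears fully on the three self-reported abstinence outcomes: 7-day at weeks 4 and 6, and 30-day at week 6. It bears only in part on the primary outcome, where it affects the self-report step and leaves a residual gap of unknown size among infrequent users.

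The size depends on the share of men who use other tobacco, which is not stated. On assumed shares of 1% to 10% per arm, the number needed per group moves from 265 to between 289 and 524 for an unverified outcome, and by less for the verified one. The weekly-smoker effect is from about 0% to 37% per 7-day window, depending on assumed timing, with 16% in the intermediate case. It concerns the 7-day secondary outcome only. The correction is worth making because it is cheap, but these calculations do not show that the primary comparison is invalid.

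**What to change.** Define quit failure, 7-day abstinence and 30-day abstinence by use of any smoked tobacco product, and word the weekly item to match, so that Eligibility Criteria, Primary Outcome Measure, Secondary Outcome Measures and Data Collection agree.

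Follow-up was completed by June 2019 (Trial Status), so the form cannot be changed for the pilot. For those data:

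- report the cigarette-only wording as a limitation, chiefly for the self-reported outcomes;
- show 7-day abstinence separately for men who were daily smokers at baseline, using the smoking frequency listed under Baseline Assessment;
- carry the corrected definition and form item into the main trial, and bear the limitation in mind when the pilot percentages are used to size it.

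The cost is a change to the outcome definitions and one form item, plus one extra table for the pilot. The downside is slightly lower reported abstinence.
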